## Abstract

**Introduction::**

The presence of significant pain and swelling during the acute stage following total knee arthroplasty (TKA) may limit the patients’ ability to cooperate in intensive physiotherapy interventions. Low-intensity pulsed ultrasound is one of the modalities that can be used for acute pain and swelling management. However, only one study investigated the effect of this modality in patients with TKA. There is limited documentation of the effects of combining low-intensity pulsed ultrasound in TKA rehabilitation in the recovery of physical impairments and how these influence the recovery of function after TKA. Therefore, this study is proposed with the aim to evaluate the effects of low-intensity pulsed ultrasound as an adjunct to conventional physiotherapy on the recovery of physical impairments, functional performance and quality of life after TKA surgery.

**Methods::**

This is an assessor-blinded quasi-experimental study comparing two approaches of physiotherapy, namely pulsed ultrasound-added physiotherapy and conventional physiotherapy. Total number of participants with TKA required for this study will be calculated based on the result of a pilot study. Participants will be alternately allocated into either pulsed ultrasound-added physiotherapy group (low-intensity pulsed ultrasound and conventional physiotherapy) or control group (conventional physiotherapy). Pulsed ultrasound-added physiotherapy group will receive low-intensity pulsed ultrasound starting at post-operative day 2 (4–5 times for the first-week after surgery and 2–3 times a week for a further 2 weeks). Both groups will receive conventional physiotherapy 4 to 5 times for the first-week after surgery and 2 to 3 times a week for a further 11 weeks. This procedure and process will be tested and established in a pilot study. Primary outcomes of interest are pain level, swelling, active range of knee motion, and quadriceps strength. The secondary outcomes are functional performance and quality of life.

**Discussion::**

This study will fill the gaps in knowledge relating the benefits of including low-intensity pulsed ultrasound into conventional physiotherapy for patients with TKA.

**Trial registration::**

Australian New Zealand Clinical Trials Registry, ACTRN12618001226291

## Introduction

1

In Malaysia, Community-Oriented Program for the Control of Rheumatic Diseases (COPCORD) survey found that 15.4% of 2594 Malaysians were diagnosed with knee osteoarthritis (OA) and more than half of 64.8% respondents with knee pain had OA-related knee pain.^[1]^ The high incidence of knee OA has been reported in countries around the world.^[2–4]^

Patients with knee OA may receive electrotherapy,^[5,6]^ joint mobilization,^[7]^ therapeutic exercises,^[8]^ virtual reality-based therapy,^[9]^ or intra-articular injection of hyaluronic acid^[10]^ to reduce pain and/or to improve functional ability. However, total knee arthroplasty (TKA) is recommended as an intervention for managing severe knee OA^[11]^ or when the conservative treatments have failed.^[12]^ The TKA followed by post-operative rehabilitation interventions namely exercises, education, dietary advice, use of insoles, and pain medication has been shown as beneficial to reduce pain and improve function of patients with moderate-to-severe knee OA.^[13]^ The patients after TKA demonstrated excellent and good early functional outcomes.^[14]^

Previous studies have shown that the recovery of physical impairments after TKA which consist of pain,^[15–17]^ knee swelling,^[18,19]^ limitation of knee range of motion,^[15,19,20]^ and quadriceps weakness^[16,19,20]^ varies. Pain^[17]^ and swelling^[18,21]^ after TKA were shown to lead to the development of quadriceps weakness and limitation of knee range of motion.^[20]^ These problems can result in reduced functional performance.^[18,21,22]^ The pain experience and decreased knee mobility after TKA may further weaken the muscles and prevent the patients from being independent in functional activities.^[17]^ A study stated that pain control at early stage of acute recovery is important to improve physical function after TKA.^[23]^ Thus, it is essential to address acute post-operative pain and swelling in order to optimize effectiveness of other interventions and improve functional recovery after TKA.

Past studies had explored the effects of adjunct modalities such as cryotherapy^[24,25]^ transcutaneous electrical nerve stimulation (TENS)^[26]^ and music therapy^[27,28]^ on recovery from pain following TKA. Cryotherapy is a common method used for patients with TKA in reducing acute post-operative pain and swelling. However, the evidence on the effects of cryotherapy remains inconclusive. Markert^[24]^ reported in general evidence shown that cryotherapy did not significantly help to reduce knee swelling, decrease in blood loss and improve range of motion of the operative knee. However, the researcher believed that cryotherapy is still useful for patients with TKA; there is evidence that the cold and compression effect provide positive outcomes. Besides, a review study^[29]^ reported that although some benefits have been shown from the use of cryotherapy following TKA, it is still inconclusive due to the limited number of Level 1 studies to support the use of cryotherapy. Another review study^[25]^ reported that most of previous studies showed positive findings on the use of cryotherapy after knee arthroplasty such as reduced pain and the use of analgesic, and improved knee range of motion and patients’ satisfaction. The study also recommended an application of cryotherapy for knee arthroplasty patients. Despite this, the researchers still highlighted that several studies did not show a significant positive effect of the application of cryotherapy.

Recently, another modality, namely pulsed ultrasound with low-intensity has been found useful in the acute management of patients with TKA. The therapy was also not stated as a contraindication for the patient with metal implants.^[30]^ However to date, this finding was reported only in one study.^[31]^ The researchers^[31]^ investigated the effect of combining low-intensity pulsed ultrasound with cryotherapy on recovery of joint function and the inflammatory index C-reactive protein in female patients with TKA. No adverse effects were reported, indicating that the modality is safe to be used on patients with TKA. The researchers found that patients who received low-intensity pulsed ultrasound in combination with cryotherapy shown greater improvement in the recovery of joint function, knee range of motion and reduction of inflammation compared to patients who received cryotherapy or low-intensity pulsed ultrasound alone. However, the study did not look into the effect of the adjunct modality on the recovery of all physical impairments which also include pain, swelling and quadriceps weakness during early stage post-TKA and how these influence the recovery of function in the post-acute phases. Further resources for acute management after TKA are needed to improve acute pain control^[32]^ and future research on the effect of impairment-targeted interventions in acute hospital and inpatient rehabilitation setting is recommended.^[33]^

The objective of this quasi-experimental assessor-blinded study is to evaluate the effects of low-intensity pulsed ultrasound as an adjunct to conventional physiotherapy on the recovery of physical impairments, functional performance and quality of life in patients with TKA. This study also intends to assess the influence of the recovery of physical impairments following Pulsed ultrasound-added physiotherapy on functional performance and quality of life of patients with TKA.

## Methods

2

### Study design and setting

2.1

This is a quasi-experimental assessor-blinded study comparing two approaches of physiotherapy, namely Pulsed ultrasound-added physiotherapy group or control group with the participant's allocation ratio is 1:1. This study will be conducted at orthopedic wards and physiotherapy department in the Universiti Kebangsaan Malaysia Medical Centre, Kuala Lumpur, Malaysia. The flow of the study is shown in Figure 1. The process in this study will be first tested in a pilot study, following which a main study will be conducted.

**Figure 1 F1:**
[figure not shown]
Flow chart of the study. TKA = total knee arthroplasty, OA = osteoarthritis.

### Study participants

2.2

Inclusion criteria are as follows:

1.Aged 50 to 80 years.2.Patients who are listed for TKA surgery due to knee OA.3.The TKA with posterior stabilized cemented total knee replacement.4.Patients who reported able to walk and climb up and down stairs with or without walking aids.

Exclusion criteria are as follows:

1.Any contraindications to pulsed ultrasound (e.g., malignancy at the tissue to be treated, bleeding at the area of the surgery and deep vein thrombosis).2.Coexistence or history of diseases which might limit the physical function and functional performance such as old fractures in the lower limb, neurology conditions (e.g., stroke), and other musculoskeletal problems.3.Has TKA complication(s) such as myocardial infarction, deep vein thrombosis, septic arthritis and neurological deficit due to regional anesthesia complications.

### Participants allocation

2.3

A systematic allocation method is used to allocate participants alternately into either pulsed ultrasound-added physiotherapy group or control group. The first participant is allocated to one of the groups at random (sealed envelopes) by a research assistant who is blinded from the intervention groups. Then, the next participant will be allocated to the other, and the process continues.

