**Table 2 T2:**
[figure not shown]
Home exercise program (Universiti Kebangsaan Malaysia Medical Center).

The treating physiotherapists and participants are not blinded to the group allocations and interventions. The practicality of this process will also be tested in the pilot study. The pilot study is conducted for 3 weeks and all participants of both groups in the pilot study are treated 4 to 5 times for the first-week post-TKA and 2 to 3 times a week for a further 2 weeks. Any amendments to the procedure and process of the pilot study will be reported and justified before implementation into the main study.

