### Assessment of outcomes

2.6

Two days prior to TKA surgery, a researcher will verbally invite potential participants and briefly explain the purpose and procedure of the study before distributing the information sheets to them. At post-operative day 2, the participants will be further screened for eligibility and an informed consent will be obtained from patients who are eligible and agreed to participate. Once recruited, the socio-demography, information of height, weight and body mass index (BMI) of the participants will be recorded. The dose of analgesic medication used will be obtained from patients’ medical record (in-patient) and based on the patients’ report (out-patient).

All participants will undergo baseline assessments before allocated alternately into the two groups at post-operative day 2 for physical impairments, and quality of life following removal of drainage tubes and discontinuation of patient-control analgesia. Baseline assessment for functional performance will be performed at week 1 after the surgery.

Assessment of outcomes following intervention will be conducted at 4 assessment time points which are at week 1, 4, and 12 following TKA surgery and at 3-month follow-up (6 months after the surgery). Outcomes on physical impairments will be assessed at the end of week 1, 4, and 12 following the surgery and at 3-month follow-up. Whereas, outcome on the functional performance will be assessed at week 4 and 12 after the surgery and at 3-month follow-up. Finally, the interventions’ outcome on quality of life of the participants will be assessed at 3-month follow-up or 6-month post-surgery.

A trained physiotherapist who is blinded to the participants’ group allocation is responsible to conduct and record all assessments. To avoid recall bias, the recorded measurements of patient's pre-intervention status will not be accessible to others during the patient's post-intervention assessment.

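### Alternation makes every allocation after the first foreseeable at day-2 enrolment and leaves the assessor blinding fragile

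*Protocol article*

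**What the plan says.** Section 2.3 (Participants allocation) sets the rule: "A systematic allocation method is used to allocate participants alternately into either pulsed ultrasound-added physiotherapy group or control group". It goes on: "The first participant is allocated to one of the groups at random (sealed envelopes) by a research assistant who is blinded from the intervention groups". After that no chance element remains: "Then, the next participant will be allocated to the other, and the process continues". Section 2.1 gives the ratio ("the participant's allocation ratio is 1:1"), names a single medical centre, and describes the study as quasi-experimental and assessor-blinded.

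Section 2.6 (Assessment of outcomes) places the enrolment decision late: "At post-operative day 2, the participants will be further screened for eligibility and an informed consent will be obtained from patients who are eligible". Baseline assessment of impairments and quality of life, and then allocation, also fall at day 2. One trained physiotherapist, blinded to group, conducts all assessments. Pre-intervention records are kept out of reach at later assessments to avoid recall bias.

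Section 2.4, below Table 2, adds: "The treating physiotherapists and participants are not blinded to the group allocations and interventions".

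Section 2.8 plans a mixed model ANOVA with time, group and interaction effects, and names no covariates.

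**The concern.** Under alternation, whoever knows the last participant's group knows the next one's. That knowledge is available while the next patient is still being screened and asked for consent, two days after surgery, when early pain, swelling and general condition can be seen. A patient with a poor outlook could be passed over, encouraged less, or taken after another patient so as to fall into the other group. If two patients reach day 2 together, choosing their order chooses their groups without excluding anyone.

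Two things are at stake. The first is comparability of the groups on prognosis, especially on factors that nobody records. The second is the assessor blinding. It is the only blinding safeguard on the outcomes, and knee circumference, goniometry and hand-held dynamometry all depend on how the assessor measures or encourages.

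**Working it through.** **1. How much is fixed in advance.** Input: pilot of 10 per group (section 2.7), so N = 20. The documents give no main-study N.
- Share of allocations determined by the first: (N − 1)/N = 19/20 = 95%. For assumed N of 40, 60 and 100 it is 97.5%, 98.3% and 99.0%.
- Possible sequences: 2. Balanced 1:1 sequences of length 20: C(20,10) = 184,756.

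**2. Whether the next group can be known at enrolment.** Section 2.3 makes the next group the opposite of the last. Section 2.4 leaves the last group visible to the treating therapist and the participant. Section 2.1 puts everyone at one centre. Section 2.6 puts final eligibility and consent immediately before allocation. Together these make the next group foreseeable when enrolment is decided. The sealed envelope in section 2.3 covers the first participant only.

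**3. What one disclosure reveals to the assessor.** Under alternation, one known group plus the entry order reveals 100% of the others, past and future. Under simple randomisation it reveals none. The assessor probably knows the entry order, because the same physiotherapist makes every baseline assessment just before allocation. Withholding pre-intervention records addresses recall, not group identity.

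**4. Who allocates.** Section 2.3 says the first allocation is made "by a research assistant who is blinded from the intervention groups". Its next sentence names nobody. Whoever carries on the alternation needs to know which group came last, and the text does not say who that is or how that person could stay blinded to group.

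**5. Illustration of size.** The documents state no figure on this point, so there is none to reproduce. Assumptions, none from the documents: no true effect; the worst fraction q on a prognostic factor is passed over whenever one particular arm is next; the factor correlates 0.5 with the outcome; outcome SD is 1; a simple two-sided comparison at one time point.
- Shift = 0.5 × φ(z_q)/(1 − q).
- q = 0.10: 0.5 × 0.1755/0.90 = 0.0975 SD.
- q = 0.20: 0.5 × 0.2800/0.80 = 0.175 SD.
- SE = √(2/n): 0.2236 for n = 40 and 0.1768 for n = 64.
- Error = 1 − Φ(1.96 − shift/SE) + Φ(−1.96 − shift/SE).

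| q | n per arm | shift/SE | error at nominal 5% |
|---|---|---|---|
| 0.10 | 40 | 0.436 | 7.2% |
| 0.10 | 64 | 0.552 | 8.6% |
| 0.20 | 40 | 0.783 | 12.3% |
| 0.20 | 64 | 0.990 | 16.8% |

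The result depends heavily on the inputs. Suppose instead that 10% are passed over in each direction and the factor is the outcome itself. The shift is then 2 × 0.195 = 0.39 SD, and the error is about 14% at 10 per arm, 33% at 30 and 50% at 50. In every case the shift does not shrink as n grows, so a larger study makes a false positive more likely.

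**6. What blocks would leave.** Take an observer who knows all past groups and the block size. For blocks of 4, expected correct guesses are 1/2 + 2/3 + (1/3)(2) + (2/3)(1.5) = 2.833, or 70.8%. For blocks of 6 and 8 the same counting gives 68.3% and 66.6%. Under alternation with N = 20 it is (19 + 0.5)/20 = 97.5%. Varying, undisclosed block sizes lower the block figures.

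**The case against.** The strongest defence is that the article hides nothing. It calls the study quasi-experimental and describes alternation openly, so the allocation is not misdescribed, and the remedy changes the type of design. That stands. But the label does not restore concealment, and the article still relies on assessor blinding. No obstacle to randomising is stated.

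A reader might also infer stronger things that the documents do not support:
- *That recruitment will be steered.* The text shows opportunity only.
- *That analysis could never repair the bias.* Pain and swelling are measured before allocation, so selection on those recorded values could in principle be handled by covariate adjustment. Only bias on unmeasured factors, such as frailty, is beyond repair. The planned ANOVA does not make that adjustment, so the measured part is not already covered.
- *That assessor blinding fails as soon as one group is known.* The entry order is needed too, and nothing says the assessor is told any assignment. Participants could disclose their own group under any method; alternation changes how much one disclosure reveals.
- *That the assistant's blinding is impossible.* The assistant is named for the first participant only, and being blinded could mean handling coded groups. The statement is unclear, not shown to be false.
- *That the error rate will be 12% or 17%.* The screening fractions, correlation and arm sizes are assumed, and the simple test is not the planned repeated-measures analysis.

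**Conclusion.** The point holds as a design weakness that should be corrected before the main study recruits. Every allocation after the first is determined (19 of 20 in the pilot), and the next one can be foreseen when eligibility and consent are decided. Selective enrolment or ordering is therefore possible, and any bias on unmeasured factors would be permanent. The assessor blinding is fragile rather than broken. This rests on the stated allocation rule, the day-2 timing, the single site and the unblinded therapists and participants. The inference about the assessor further assumes knowledge of the entry order, which is likely but not stated. The error rates of about 7–17% show only what modest steering could do under the assumed inputs; they are not an estimate for this trial. No sample size, power or significance level in the article is shown to be wrong.

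**What to change.** For the main study, replace alternation with a computer-generated 1:1 sequence in permuted blocks of randomly varying, undisclosed size. It should be prepared by someone not involved in recruitment or assessment and held in sequentially numbered, opaque, sealed envelopes. Open each envelope only after day-2 eligibility, consent and baseline assessment have been recorded. Keep the sequence and block sizes from the recruiter and the assessor. State who allocates, and clarify in what sense the allocating assistant is blinded.

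The cost is one list, a set of envelopes, and an ethics and registry amendment; no visits or staff are added. Sealed envelopes are already in use for the first participant, and section 2.4 provides for justified changes between pilot and main study. The downsides are slightly unequal group sizes and some remaining guessability, because therapists are unblinded and see past assignments.

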### Interventions

2.4

The interventions in this study will be conducted for 12 weeks. The Pulsed ultrasound-added physiotherapy group will receive low-intensity pulsed ultrasound and conventional physiotherapy, while the control group will receive conventional physiotherapy alone. Pulsed ultrasound-added physiotherapy and control groups will receive conventional physiotherapy interventions 4 to 5 times for the first-week post-TKA and 2 to 3 times a week for a further 11 weeks. Besides, the application of low-intensity pulsed ultrasound (4–5 times for the first-week after surgery and 2–3 times a week for a further 2 weeks) in the pulsed ultrasound-added physiotherapy group will be started at post-operative day 2.

The conventional physiotherapy that will be used in this study is based on the therapy program for TKA implemented in the Universiti Kebangsaan Malaysia Medical Centre and also based on evidences which showed that exercise interventions which include stretching, strengthening,^[34]^ and functional exercises provide better outcome in recovery following TKA.^[35–37]^ The rehabilitation program for TKA is shown in Table 1.

**Table 1 T1:**
[figure not shown]
Rehabilitation program for TKA (Universiti Kebangsaan Malaysia Medical Center).

Low-intensity pulsed ultrasound (GYMNA Pulson 330, Netherlands) will be administrated for 5 minutes with the pulse ratio of 1:4 (20% duty cycle); 3 MHz frequency; and the intensity will be determined based on the thickness of the individual patient's tissues. The designated surgeon will measure the thickness of tissues using patella caliper during the surgical procedure. The area to be treated is the medial aspect of the knee which is about 1 cm away from the medial border of the patella. Transducer head and any equipment related to the pulsed ultrasound treatment will be cleaned with alcohol-based swab before and after the application.

All participants will be instructed to do home exercise program 2 times per day. The home exercise program is adopted from an exercises program for knee surgery used by physiotherapy in the university medical center (Table 2). Once-per-week telephone call will be attempted for each participant to remind them to do the home exercises program and to monitor their progression and potential adverse effects related to exercise such as cramps and muscle soreness. Exercises diary will be provided to all participants to record their home exercises practice.

**Table 2 T2:**
[figure not shown]
Home exercise program (Universiti Kebangsaan Malaysia Medical Center).

The treating physiotherapists and participants are not blinded to the group allocations and interventions. The practicality of this process will also be tested in the pilot study. The pilot study is conducted for 3 weeks and all participants of both groups in the pilot study are treated 4 to 5 times for the first-week post-TKA and 2 to 3 times a week for a further 2 weeks. Any amendments to the procedure and process of the pilot study will be reported and justified before implementation into the main study.

